## Abstract

**Background:**

Post-infectious cough (PIC) refers to a type of persistent cough triggered by respiratory tract infections that remains unresolved after the initial infection is controlled. It significantly impacts daily life, work, and overall quality of life. This study aims to evaluate the clinical efficacy and safety of the Shufeng Huashi (SFHS) formula, a Traditional Chinese Medicine (TCM) compound, in patients with PIC.

**Methods and analysis:**

This multicenter, randomized, double-blind, placebo-controlled, parallel-group clinical trial will recruit 120 patients aged 18–65 who meet the diagnostic criteria for PIC. Participants will be randomly assigned to the SFHS group or the placebo group in a 2:1 ratio using a random coding table. The SFHS group will receive oral TCM treatment for 14 days, while the placebo group will receive a placebo for the same duration, both administered three times daily. The primary outcome measure is the cough relief rate on day 14. Secondary outcome measures include cough symptom scores (CSS), cough evaluation test (CET), TCM syndrome efficacy, Leicester Cough Questionnaire (LCQ) scores, cough cure rate, cough relief rate on day 7, time to cough cure, time to cough relief, and cough recurrence rate. Adverse events will be monitored and recorded throughout the study.

**Discussion:**

PIC is highly prevalent, yet current pharmacological treatment options remain limited. This trial is expected to generate evidence regarding the efficacy and safety of TCM in treating PIC and inform evidence-based recommendations for clinical practice.

**Clinical trial registration:**

https://itmctr.ccebtcm.org.cn/mgt/project/view/2038531670868623360, Identifier ITMCTR2025001210.

## Introduction

1

Post-infectious cough (PIC) is characterized by a persistent cough that remains unresolved after the acute symptoms of a respiratory tract infection have subsided. It typically lasts for 3 to 8 weeks, while chest imaging remains normal (1). PIC is one of the most common types of chronic cough and stands as the leading cause of subacute cough (2). Adults typically experience 2–3 episodes of the common cold per year (3), with an incidence of influenza of 10.7% (4); moreover, the frequency of common colds tends to increase as immunity declines. Approximately 11 to 25% of adults develop PIC following a respiratory infection, a rate that can soar to 50% during epidemic seasons (5). Patients with a prior history of PIC are more likely to develop persistent cough after subsequent infections. The course of the disease significantly impairs patients’ work and quality of life, potentially leading to complications or misdiagnosis, which imposes unnecessary economic burdens and psychological distress. Current treatments for PIC primarily involve symptomatic relief using antitussives, antihistamines combined with decongestants. However, evidence supporting the efficacy of these regimens remains weak (1). Furthermore, these medications often entail unavoidable side effects such as somnolence and decreased appetite, and recurrence is common after discontinuation (6). Consequently, identifying an effective therapeutic approach with minimal side effects has become a focal point of current PIC research.

Traditional Chinese Medicine (TCM) offers distinct advantages in treating diseases through syndrome differentiation and holistic regulation. In the management of PIC, TCM has demonstrated significant efficacy in shortening cough duration and improving patients’ quality of life, characterized by high safety profiles and low recurrence rates (7). Our research group previously developed the Suhuang Zhike Capsule based on the “Wind-type Cough” theory proposed by National TCM Master [name]. Composed of Herba *Ephedrae Herba* (Mahuang), *Cicadae Periostracum* (Chantui), *Perillae Folium* (Zisuye), *Perillae Fructus* (Zisuzi), *Schisandrae Chinensis Fructus* (Wuweizi), *Arctii Fructus* (Niubangzi), *Peucedani Radix* (Qianhu), *Eriobotryae Folium* (Pipaye), *Pheretima* (Dilong), this formula has shown remarkable therapeutic effects on PIC dominated by Wind-evil. It significantly improves the overall response rate and reduces cough severity (8). Consequently, it has been recommended in the Guidelines for Diagnosis and Treatment of Cough (9) as a therapeutic option. Previous pharmacological studies indicate that Suhuang Zhike Capsule improves inflammation in the airways and lung tissues (10–12). By regulating the neuro-immune network, it downregulates the levels of Substance P (SP) and Calcitonin Gene-Related Peptide (CGRP) in bronchoalveolar lavage fluid. Furthermore, it suppresses airway inflammation and the release of inflammatory mediators, thereby reducing cough receptor stimulation and decreasing cough frequency (13).

In recent years, changes in disease spectrum and modern lifestyle patterns have led to an increasing prevalence of internal dampness in patients with PIC, superimposed on the underlying pathogenesis of Wind-evil invading the lungs. Clinically, these patients present with features of latent wind invasion, such as coughing triggered by irritant odors or excessive talking, and pharyngeal itching, together with signs of dampness stagnation, including decreased appetite, abdominal distension, and a sticky oral sensation. Accordingly, based on the “Wind-type Cough” theory, our research group has proposed the syndrome termed Wind invasion with Dampness obstruction (hereafter abbreviated as Wind invasion-Dampness obstruction syndrome). The Shufeng Huashi (SFHS) formula was subsequently developed by modifying the original Suhuang Zhike Decoction to include additional dampness-resolving medicinal herbs. This study aims to evaluate the efficacy and safety of the SFHS formula in alleviating symptoms and improving outcomes for patients with PIC.

## Methods

2

### Study design

2.1

A randomized, double-blind, placebo-controlled, parallel-group, superiority clinical trial design will be employed. The study will be conducted across six hospitals in three regions of China: China-Japan Friendship Hospital (Beijing), the Third Affiliated Hospital of Beijing University of Chinese Medicine (Beijing), Wangjing Hospital of the China Academy of Chinese Medical Sciences (Beijing), Huairou Hospital of Beijing Traditional Chinese Medicine Hospital (Beijing), Wuqing District People’s Hospital (Tianjin), and the Affiliated Traditional Chinese Medicine Hospital of Southwest Medical University (Sichuan). Trial monitoring will be conducted on-site, with each study center receiving an initiation visit, a close-out visit, and two routine monitoring visits.

The overall study period spans from November 2024 to November 2027. The initial phase (November 2024 to October 2025) was devoted to protocol development and trial preparation, with no participant enrollment or screening conducted prior to the receipt of ethical approval and trial registration. Participant recruitment and intervention are scheduled between November 4, 2025, and November 30, 2027. The detailed study flow is illustrated in Figure 1. This protocol adheres to the SPIRIT 2025 guidelines and is conducted in accordance with the ethical principles outlined in the Declaration of Helsinki.

**Figure 1 fig1:**
[figure not shown]
Study flowchart.

Ethical approval has been granted by the Clinical Research Ethics Committee of China-Japan Friendship Hospital (Approval No. 2025-KY-125-1). Any amendments to the trial protocol require submission to and re-approval by the Committee prior to implementation, and will be updated in the trial registry in a timely manner. This study is a joint research project sponsored by the China Association of Chinese Medicine and funded by Guangdong Efong Pharmaceutical Co., Ltd. Notably, the funder will not be involved in the study design, data collection and management, or data analysis. Participant recruitment for this trial is ongoing, and written informed consent has been obtained from all participants. The trial will be reported in compliance with the CONSORT guidelines and has been registered with the International Traditional Medicine Clinical Trial Registry (Identifier: ITMCTR2025001210; available at: https://itmctr.ccebtcm.org.cn/mgt/project/view/2038531670868623360). The detailed schedule for interventions and assessments is provided in Table 1.

**Table 1 tab1:** Study schedule.

Items	Screening (day −3 to Day 0)	Baseline (day 0)	Visit 1 (day 7 ± 1)	Visit 2 (day 14 ± 1)	Telephone follow-up (day 21 ± 1)
Written informed consent	√				
Collection of demographic data	√				
Medical history (past 3 months)	√				
Concomitant diseases and symptoms	√				
Vital signs	√		√	√	
Pulmonary auscultation	√		√	√	
Concomitant medications	√	√	√	√	√
CSS	√		Based on diary card records		√
CET	√		√	√	
TCM syndrome score	√		√	√	
LCQ	√			√	
Complete blood count	√			√	
Urinalysis	√			√	
Liver and renal Function tests	√			√	
12-Lead Electrocardiogram	√			√	
Chest X-ray or chest CT	√				
Pulmonary function test (including bronchodilator test)	√				
Serum pregnancy test (women of childbearing age)	√			√	
Adverse event recording		√	√	√	√
Randomization		√			
Dispensation of study medication		√			
Dispensation of diary card		√			
Return of study medication				√	
Return of diary card				√	
Compliance assessment			√	√	

### Randomization and blinding

2.2

A block randomization method will be employed, with the randomization sequence generated by a statistician independent of the study conduct. Using an appropriate block length and a predefined random seed, a randomization sequence for 120 subjects will be generated via SAS 9.4 statistical software. Participants will be assigned to either the SHFS or placebo group at a 2:1 ratio. A randomization table will be generated, listing the drug kit numbers for assignment. Investigators will allocate these numbers to participants in the order they enroll, starting from the lowest number. A competitive enrollment mechanism will be implemented across all participating centers. This study is a double-blind trial; therefore, both investigators and outcome assessors will be blinded to the treatment allocation sequence. The investigational drug and the corresponding placebo will be identical in appearance and packaging. The blinding codes will be prepared in triplicate, sealed, and securely stored by the lead clinical research institution, the statistical unit, and the sponsor, respectively. Unauthorized access to blinding or emergency envelopes is strictly prohibited. Any premature unblinding of the codes will result in the disqualification of the clinical trial. Unblinding will be performed once, at the end of the trial or when necessary for safety reasons.

### Participants

2.3

In this trial, PIC is defined according to the following criteria: (1) History of infection: A history of respiratory tract infection prior to the onset of cough. (2) Clinical manifestations: Presence of an irritant dry cough or a small amount of white, viscous sputum. (3) Duration: Cough typically persists for a period of 3 to 8 weeks. (4) Imaging findings: No significant abnormalities detected on chest X-ray or CT scan. (5) Differential diagnosis: Exclusion of cough caused by other underlying etiologies (e.g., cough-variant asthma, upper airway cough syndrome, or gastroesophageal reflux-induced cough).

The detailed diagnostic criteria for the Wind invasion-Dampness obstruction syndrome are provided in Table 2. The Cough Symptom Score (CSS) is divided into two components: daytime and nighttime scores. Based on the intensity and frequency of the cough, as well as the degree of its impact on the patient’s sleep and daily activities, the symptoms are categorized into four grades, scored from 0 to 3. The total CSS is defined as the sum of the daytime and nighttime scores (Table 3).

**Table 2 tab2:** Diagnostic criteria for Wind invasion-Dampness obstruction syndrome.

Category	Symptoms and signs
Primary symptoms	① Cough ② Throat itching or discomfort ③ Sudden onset or exacerbation triggered by temperature changes (cold or heat), irritant odors, or similar factors
Secondary symptoms	① Sticky sensation in the mouth ② Loss of appetite ③ Abdominal distension
Tongue signs	Pale tongue with white moist or white greasy coating
Pulse signs	Floating pulse, floating-moderate pulse, floating-soft pulse, floating-slippery pulse, floating-thin pulse, or normal pulse

The syndrome is diagnosed when the primary symptom is present, ≥2 secondary symptoms are met, together with corresponding tongue and pulse signs.

**Table 3 tab3:** Cough symptom score.

Daytime	Nighttime
□0 points: No cough	□0 points: No cough
□1 point: Occasional brief cough	□1 point: Brief cough at sleep onset or occasional nocturnal cough
□2 points: Frequent cough, mildly affecting daily activities	□2 points: Cough mildly affecting nighttime sleep
□3 points: Frequent cough, severely affecting daily activities	□3 points: Cough severely affecting nighttime sleep

#### Inclusion criteria

2.3.1

Participants who meet all of the following criteria will be eligible for enrollment:

(1) Age: Aged 18–65 years (inclusive) at the time of informed consent.(2) Western Medicine Diagnosis: Meeting the diagnostic criteria for PIC.(3) TCM pattern identification: Wind invasion-Dampness obstruction syndrome.(4) Symptom Severity: CSS of ≥ 3.(5) Informed consent: Written informed consent was obtained.

#### Exclusion criteria

2.3.2

Participants meeting any of the following criteria will be excluded from the trial:

(1) Other causes of cough: Cough caused by cough-variant asthma, upper airway cough syndrome, eosinophilic bronchitis, gastroesophageal reflux cough, atopic cough, chronic bronchitis, or other underlying etiologies; or persistent cough symptoms prior to the current infection.(2) Severe pulmonary diseases: Presence of severe respiratory conditions such as chronic obstructive pulmonary disease, lung cancer, or pulmonary tuberculosis.(3) Medication history: Use of angiotensin-converting enzyme inhibitors (ACEIs) within the past month.(4) Smoking status: Current smokers or those who have quit smoking for less than 3 months.(5) Comorbidities: Concurrent severe cardiovascular or cerebrovascular diseases, malignant tumors, hematological or hematopoietic system diseases, gastrointestinal diseases, or other severe or progressive systemic diseases; or severe mental illness or cognitive impairment rendering the participant unable or unwilling to cooperate.(6) Hepatic or renal impairment: Alanine aminotransferase (ALT) or aspartate aminotransferase (AST) > 2 times the upper limit of normal (ULN); and/or serum creatinine (Cr) > 1.5 times the ULN.(7) Abnormal laboratory findings: White blood cell (WBC) count <3.0 × 10^9^/L or >10.0 × 10^9^/L; and/or neutrophil percentage >80%.(8) Body temperature: Axillary temperature ≥37.3 °C.(9) Allergies: Known hypersensitivity to two or more substances, or allergy to the study drug or its ingredients.(10) Substance abuse: History of long-term alcohol or drug abuse.(11) Pregnancy and lactation: Women who are pregnant, breastfeeding, or planning to become pregnant.(12) Other trials: Participation in other clinical trials within the past 3 months.(13) Other concerns: Any other conditions that the investigator deems inappropriate for participation (e.g., poor compliance).

### Interventions

2.4

Due to the lack of high-quality, strongly recommended pharmacological treatments for PIC, and considering its self-limiting nature where spontaneous remission often occurs, a placebo control was selected. The placebo is a simulated version of the SFHS granules. Study participants will be randomized into either the treatment group or the control group. The treatment group will receive SFHS granules, while the control group will receive SFHS simulators (placebo). Both will be administered orally, three times daily, for a continuous duration of 14 days. Both the SFHS granules and their corresponding placebos are manufactured by Guangdong Efong Pharmaceutical Co., Ltd. All medications were identical in appearance and packaging, and were labeled in a blinded manner. Each code corresponds to a unique drug allocation number in the randomization list. Each medication box contains 48 sachets (42 g per sachet) of either SFHS granules or the placebo, dispensed in a single batch upon completion of screening and enrollment. During subsequent follow-up visits, the number of used empty packages and remaining medications will be recorded to monitor compliance.

SFHS granules consist of *Ephedrae Herba* (Mahuang), *Armeniacae Semen Amarum* (Kuxingren), *Cicadae Periostracum* (Chantui), *Perillae Fructus* (Zisuzi), *Peucedani Radix* (Qianhu), *Arctii Fructus* (Niubangzi), *Stemonae Radix* (Baibu), *Acori Tatarinowii Rhizoma* (Shichangpu), *Magnoliae Officinalis Cortex* (Houpo), *Citri Reticulatae Pericarpium* (Chenpi), *Atractylodis Rhizoma* (Cangzhu), *Angelicae Sinensis Radix* (Danggui), and *Glycyrrhizae Radix et Rhizoma* (Gancao). The placebo contains starch, dextrin, and 5% SFHS granule components to ensure similarity to the SFHS granules in color, odor, taste, shape, and texture.

### Concomitant treatment

2.5

Symptomatic treatments for comorbidities are permitted provided that they do not interfere with the evaluation of efficacy and safety. The generic name (or name of the therapy), dosage, rationale for use, frequency, and duration of such treatments are required to be meticulously documented in the medical records and electronic Case Report Forms (eCRF) for subsequent analysis and reporting during data synthesis. The use of other Western medicines, Traditional Chinese Medicine, or Chinese patent medicines with antitussive effects or therapeutic functions similar to the investigational drug is strictly prohibited.

### Outcomes

2.6

#### Primary outcome

2.6.1

The primary outcome measure is the cough relief rate after 14 days of treatment. Cough relief is defined as a total CSS (daytime + nighttime) ≤ 2, sustained for at least 48 h ± 2 h. Cough cure is defined as a total CSS (daytime + nighttime) ≤ 1, sustained for at least 48 h ± 2 h. The CSS will be recorded at baseline and daily throughout the study. The inter-group difference in the 14-day cough relief rate will be evaluated according to these diagnostic criteria.

#### Secondary outcomes

2.6.2

(1) CSS: CSS will be recorded at baseline and daily. The differences in CSS between the two groups will be evaluated on day 7 and day 14.(2) CET: CET scores will be recorded at baseline, day 7, and day 14 to evaluate the inter-group differences in CET scores at these time points.

The Cough Evaluation Test (CET) is a concise, patient-reported questionnaire comprising 5 items that assess key dimensions of cough impact, including daytime cough frequency, sleep disturbance, cough intensity, interference with work and daily activities, and cough-related anxiety. Each item is rated on a 5-point Likert scale from 1 (never) to 5 (always/frequently). The total score ranges from 5 to 25, with higher scores indicating more severe cough-related impairment.

(3) TCM Syndrome Efficacy: TCM syndrome scores will be recorded at baseline, day 7, and day 14 to assess the inter-group differences in both the scores and the overall clinical efficacy of TCM syndromes.

The TCM syndrome score is an instrument used to assess the severity of symptoms associated with the Wind invasion-Dampness obstruction syndrome. It comprises three major symptoms—cough, throat discomfort, and symptom aggravation triggered by cold, heat, or irritant odors—and three minor symptoms, including oral stickiness, poor appetite, and abdominal distension. Major symptoms are graded on a 4-level scale (absent, mild, moderate, and severe), scored 0, 2, 4, or 6 points respectively; minor symptoms are scored 0, 1, 2, or 3 points. Tongue appearance and pulse condition are additionally recorded to confirm the syndrome diagnosis. The total score is the sum of all individual symptom scores, with higher scores indicating greater TCM syndrome severity.

(4) LCQ: LCQ scores will be recorded at baseline and on day 14 to evaluate the inter-group differences in the improvement of quality of life.

The LCQ is a health-related quality of life instrument specifically designed to assess the impact of cough across three domains: physical (8 items), psychological (7 items), and social (4 items). Each of the 19 items is rated on a 7-point Likert scale ranging from 1 to 7. Domain scores are calculated as the mean of the constituent items (range 1–7), and the total score is the sum of the three domain scores, ranging from 3 to 21, with higher scores indicating better cough-related quality of life.

(5) Cough Cure and Relief Rates: Based on daily CSS records and predefined criteria, the inter-group differences in the cough cure rate (at day 7 and day 14) and the cough relief rate (at day 7) will be evaluated.(6) Time to Cough Cure and Relief: Based on daily CSS records, the inter-group differences in the median time to reach cough cure and relief within the 14-day period will be analyzed.(7) Cough Recurrence Rate: This is defined as the proportion of participants who achieved relief by the end of treatment but experienced a recurrence of cough during the 7-day post-treatment follow-up.

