### Sample size calculation

2.7

The sample size was estimated based on efficacy data from previous clinical trials. The cough relief rate for Suhuang Zhike Capsule was reported to be 87.75–93.33% (8, 14); thus, the expected relief rate for the Shufeng Huashi formula (π_T_) was estimated at 88%. The relief rate for the placebo, based on previous studies, ranged from 47.76–58.51% (15, 16); therefore, the expected relief rate for the placebo group (π_C_) was set at 48%. A 2:1 superiority design was employed, with a two-sided significance level of *α* = 0.05 and a power of 0.9 (1 − *β* = 0.9). A clinical superiority margin of 10% was considered. Using PASS 21 software for sample size estimation, the calculated requirement was 71 participants for the treatment group and 36 for the control group. Accounting for a 10% dropout rate and potential unforeseen data loss during trial execution, a total of 120 participants will be enrolled, with 80 in the treatment group and 40 in the control group. Participants will be recruited through outpatient clinics and advertisements.

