Based on the theory of “Wind Cough,” our research group proposed the “Wind invasion-Dampness obstruction” syndrome. By modifying the Suhuang Zhike decoction with additional dampness-resolving herbs, we developed the SFHS formula (26). *Ephedrae Herba* (Mahuang) serves as the monarch herb to disperse pathogenic factors in the lung, thereby relieving cough and asthma. *Armeniacae Semen Amarum* (Kuxingren) and *Stemonae Radix* (Baibu) act as minister herbs to suppress cough and resolve phlegm, while *Atractylodis Rhizoma* (Cangzhu) and *Magnoliae Officinalis Cortex* (Houpo) strengthen the spleen and eliminate dampness. *Perillae Fructus* (Zisuzi) and *Peucedani Radix* (Qianhu) are used as adjuvant herbs, which not only enhance the wind-dispelling effect of Mahuang but also promote the coordination of ascending and descending Lung qi. *Cicadae Periostracum* (Chantui), as the courier herb, further disperses wind pathogens and helps relieve throat itching. Since 2022, this formula has been used as an institutional formula in our hospital, with over 12,000 doses administered. This study aims to evaluate the efficacy and safety of the SFHS formula in alleviating clinical symptoms and reducing the recurrence rate of PIC.

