In summary, this trial aims to evaluate the effects of the SFHS formula on cough symptoms, quality of life, and recurrence rates. By assessing both symptom relief and reduction in recurrence, the study will provide clinical evidence on the efficacy and safety of the SFHS formula in managing PIC.

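### The recurrence rate compares only participants who reached relief, a subset that treatment itself selects (about 70 vs 19), so it cannot by itself support the aim of reducing recurrence

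*Protocol article*

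**What the plan says.** Section 2.6.2 of the protocol article lists the cough recurrence rate as the last secondary outcome and defines it as "the proportion of participants who achieved relief by the end of treatment but experienced a recurrence of cough during the 7-day post-treatment follow-up". The denominator is not written out, but participants who achieved relief is the natural reading.

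Relief is the primary outcome: a total CSS of 2 or less, maintained for about 48 hours and judged at Day 14 (2.6.1 and 2.10). Section 2.7 plans for relief in 88% on SFHS and 48% on placebo, and for enrolment "with 80 in the treatment group and 40 in the control group".

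The Discussion gives recurrence an efficacy role. It names "reducing the recurrence rate of PIC" among the things the study is to evaluate, and its closing summary begins "By assessing both symptom relief and reduction in recurrence". It also says that the follow-up week is there to demonstrate sustained relief.

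For binary secondary outcomes, section 2.10 gives only general rules: a CMH test where centre effects are considered, and a risk difference with 95% CI. It says nothing about selection into the relieved subset and plans no comparison of relapse or sustained relief in all participants. Table 1 schedules one CSS after treatment, at the Day 21 telephone call; diary cards are returned at Day 14.

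**The concern.** Whether a participant enters the recurrence comparison depends on relief, and relief is what the treatment is meant to change. If SFHS works as planned, its relieved group contains many people whom placebo would not have relieved. The two relieved groups then differ in prognosis as well as in treatment, and randomisation no longer balances them. A treatment with no effect on relapse could look worse because it also relieved harder cases, or better if the additional people it relieved were less prone to relapse.

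What is at stake is the claim. A between-arm p value and risk difference on this outcome, read next to the Discussion's wording, would be taken as evidence for or against an effect on recurrence that the comparison cannot supply.

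**Working it through.** **Inputs from the protocol (2.7).** Relief 88% vs 48%; superiority margin 10 points; two-sided alpha 0.05; power 0.90; 2:1 allocation; 10% dropout; 80 and 40 enrolled. The source range for placebo relief is 47.76% to 58.51%. The protocol gives no recurrence rates, so all those below are assumptions.

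**The plan's own figure.** With unpooled variance, control n = [0.48×0.52 + 0.88×0.12/2] × (1.960 + 1.282)² / (0.40 − 0.10)² = 0.3024 × 10.51 / 0.09 = 35.3, rounded to 36. Treatment n = 70.6, rounded to 71. This reproduces "71 participants for the treatment group and 36 for the control group". Dividing by 0.9 gives 79 and 40, against 80 and 40 enrolled. The sample size is not in dispute.

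**Size of the relieved subset.**
- As enrolled: 80 × 0.88 = 70.4 and 40 × 0.48 = 19.2.
- At the calculated requirement: 71 × 0.88 = 62.5 and 36 × 0.48 = 17.3.
- At the upper placebo rate: 40 × 0.5851 = 23.4 on placebo.

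**Selection, illustration 1.** Assume half the participants are mild and half severe. Relief is 96% and 80% on SFHS (mean 88%), and 70% and 26% on placebo (mean 48%). Recurrence after relief is 10% in mild and 30% in severe cases, the same in both arms.
- SFHS: (0.96×0.10 + 0.80×0.30) / 1.76 = 0.336/1.76 = 19.1%.
- Placebo: (0.70×0.10 + 0.26×0.30) / 0.96 = 0.148/0.96 = 15.4%.
- The difference is 3.7 points against SFHS, with no effect on relapse in either stratum.
- SE = √(0.191×0.809/70.4 + 0.154×0.846/19.2) = 0.095, so the 95% half-width is 18.6 points.

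**Selection, illustration 2 (direction).** Assume that everyone relieved on placebo would also be relieved on SFHS. Then 48% are relieved on either arm and a further 40% only on SFHS. Let the first group recur at 20% whichever treatment they receive.
- If the second group recurs at 30%, SFHS shows (0.48×0.20 + 0.40×0.30)/0.88 = 24.5% against 20% on placebo.
- If it recurs at 10%, SFHS shows (0.48×0.20 + 0.40×0.10)/0.88 = 15.5% against 20%.

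The apparent effect changes sign with an assumption that the document cannot settle.

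**All participants as denominator.** With equal 20% recurrence among the relieved: 0.88×0.20 = 17.6% on SFHS and 0.48×0.20 = 9.6% on placebo. The arm that relieves more people has more who can relapse, and is penalised for it.

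**Precision at 70 vs 19.** For a common recurrence rate p, half-width = 1.96√[p(1−p)(1/70 + 1/19)], which is 15, 20 and 23 points at p = 10%, 20% and 30%.

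Power for 30% on placebo vs 15% on SFHS, by the pooled normal approximation:
- Pooled rate (10.5 + 5.7)/89 = 0.182.
- Null SE 0.0998; alternative SE 0.1135.
- Power = Φ[(0.15 − 1.96×0.0998)/0.1135] = Φ(−0.40) = 34%. Fisher's exact test gives 27%.

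For 30% vs 5% the figures are about 81% and 78%.

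**Sustained relief in all participants.** Under illustration 1, relief without recurrence is 0.5×0.96×0.90 + 0.5×0.80×0.70 = 71.2% on SFHS and 0.5×0.70×0.90 + 0.5×0.26×0.70 = 40.6% on placebo. With equal recurrence of 10%, 20% or 30% among the relieved, the comparison is 79.2% vs 43.2%, 70.4% vs 38.4% or 61.6% vs 33.6%. Power at 80/40 is about 98%, 93% and 84% (two-sided 0.05, no margin).

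**The case against.** Recurrence among responders is a legitimate descriptive outcome. It is the last of seven secondary outcomes, the trial is sized for the primary one only, and low power for a secondary outcome is not a defect. The Discussion also describes the follow-up as monitoring symptoms and assessing recurrence after withdrawal, and concedes that one week is short. The strata and recurrence rates above are assumed. The 3.7-point distortion in illustration 1 is small beside its 18.6-point half-width, and it runs against SFHS. All of this stands. It limits the point to what may be concluded from the outcome; it does not make the contrast a randomised one or remove the stated aim.

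Three stronger readings are tempting, and the document does not support them:
- That the subset is too small to detect even near-elimination of recurrence. It is not: 30% vs 5% has about 80% power, and 30% vs 1% has 93% (pooled normal) to 96% (Fisher). Power is low for moderate effects only.
- That the bias is known to flatter SFHS. Its direction cannot be established from the protocol.
- That any remaining cough counts as recurrence, which would contradict a relief definition that allows a CSS of 1 or 2. The article gives no threshold, and loss of relief is the natural meaning. This is a detail that the full protocol may hold, so it needs clarifying and is not an error.

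It can also fairly be said that sustained relief changes the question. Under illustration 1 it shows a gap of 71.2 − 40.6 = 30.6 points with no effect on recurrence at all. It therefore complements the recurrence rate and does not test recurrence alone.

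**Conclusion.** The point holds as a limit on inference. As defined, the recurrence rate compares groups formed by the treatment's own effect, expected at about 70 vs 19 under the protocol's planning rates. It cannot by itself support a statement that SFHS reduces recurrence, and changing the denominator to all participants does not rescue it. The subset sizes follow directly from section 2.7. The size and direction of the bias rest on assumed recurrence rates and strata and are not known. Precision is modest, with a half-width of about 19 points under illustration 1 (15 to 23 points for common rates of 10% to 30%). The primary analysis and the sample size are unaffected. The change is worth making because the Discussion presents reduced recurrence as an aim and the data for a randomised comparison of sustained relief are already scheduled.

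**What to change.** 1. Add a secondary comparison in all FAS participants: relief at Day 14 and a CSS of 2 or less still at Day 21, with a centre-stratified risk difference and 95% CI. State how a missing Day 21 score is handled, since carrying a relieved Day 14 score forward would count it as sustained relief.
2. Label this outcome sustained relief, which matches the stated purpose of the follow-up week. Say that it mainly reflects Day 14 relief and is not a test of recurrence alone.
3. Report the recurrence rate among relieved participants descriptively by arm, with its denominators and without a p value or causal wording.
4. Clarify that recurrence means loss of the relief criterion at Day 21, that is, a CSS of 3 or more after relief at Day 14.
5. Limit the two statements in the Discussion about reducing recurrence to what these analyses can show.

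The cost is one additional secondary analysis and a more modest claim about recurrence. No new visit or measurement is needed. Recruitment is ongoing and allocation is blinded, so the change can be made as a documented amendment before unblinding.
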